## Abstract

**Background:** Fragility fractures of the hip are a common injury in England. Meeting post-operative resting energy expenditure (REE) needs are fundamental to recovery from trauma that with greater nutritional intake, post-operative complications and length of stay can be reduced. However, dietary intake can be overlooked when the goal is prompt surgery to reduce pain and lower the risks of mortality at 30 days and 1 year. **Aims:** The primary aim of this study is to observe if post-operative dietary energy intake (kJ/kcal) of older adult hip fracture patients meets their post-operative REE needs to mobilise post-surgery. Secondly, we aim to explore if there is a relationship between length of stay, comorbidity and post-operative complications in relation to dietary intake. **Methods and analysis:** Using a weighed food method, all food and fluid intake from the day of surgery until post-operative day three inclusive will be recorded for a cohort of 30 older adult hip fracture patients. Dietary intake per day will be compared against REE and macronutrient requirements. Baseline sociodemographic and medical history data will be obtained, along with admission data such as malnutrition screening and type of fracture. Regression analysis will be used to explore associations between dietary intake, post-operative complications and length of stay where indicated and to identify if there are areas for further dietary development in this specific patient group. **Ethics and dissemination:** The Health Research Authority approved this study (REC 24/NE/0034). Findings will be published in peer-reviewed, scientific journals and presented at academic conferences.

## Introduction

Older adult hip fracture patients are a significant surgical population in England, with over 65,000 cases registered in 2022 according to the National Hip Fracture Database (NHFD) (2023a) with average 30-day mortality rates at just over 6% (NHFD, 2023b). Approaches to in-patient care has seen marked developments in recent years, including orthogeriatric assessment, surgery within 36 hours of diagnosis and early mobilisation; strategies that have been incentivised via the Best Practice Tariff (National Health Service (NHS England, 2021) and hospital key performance indicators specified by the NHFD (2023c). However, an aging population and the long-term effects of COVID-19 has increased the risk of frailty (NHFD, 2023c), morbidity and polypharmacy, which can present challenges in providing even basic care needs, including supporting nutrition and dietary intake.

Malnutrition is a modifiable risk factor, and as outlined in an earlier review by Cochrane, malnutrition is prevalent in the hip fracture population (Avenell et al., 2016). However, the review explored supplementation strategies rather than dietary intake since patients ‘may have poor food intake while in hospital’. Conversely, studies of nutritional status have repeatedly demonstrated a correlation between malnutrition and lower functional outcome (Wong et al., 2021), mortality at 3, 6 and 12 months and the presence of post-operative delirium (Zanetti et al., 2019), however, focus has been on the most appropriate nutritional screening tool as opposed to opportunities for dietary improvement.

Current guidance in relation to specific nutritional support for hip fracture patients is limited, and rather the indication for nutritional support is based on a generic risk assessment for all adults regardless of condition or injury (NICE, 2024). The NHFD has measured nutritional risk assessment compliance since 2016 (NHFD, 2017), with the Malnutrition Universal Screening Tool (MUST) most used and is currently validated by both the British Association for Parenteral and Enteral Nutrition (BAPEN) and the National Institute for Health and Care Excellence (NICE) (BAPEN, 2003; NICE, 2024).

Research exploring the specific dietary intake of older adult hip fracture patients is also limited. Most recently, a short report of weighed lunch and dinner intake (excluding fluids), found dietary intake was poor (‘nutritionally vulnerable patients’ (*n* = 15) mean (SD): 643 (354) kcal/day), regardless of ‘good nutrition practice’ according to NHS England issued guidance (Sahota et al., 2023). However, methodological quality was poor owing to the type of study, with a lack of clarity regarding how intake was assessed, and the weighed element suggested to be only ‘total plate waste’ for the ward inclusive. Additionally, whilst the study claimed to focus on nutrition practice, there was no breakdown of macronutrients other than protein and no analysis of food diary data, but rather an exploration of food waste. In an earlier study that explored the dietary intake of hip fracture patients, only 59% of energy needs were met (week 2, 3-day intake; 4219 ± 319 kJ/day, kcal not stated), however, the authors stressed the importance of ‘early nutritional assessment’ but did not commence the food diary until post-operative week 2, and excluded those with cognitive impairment, which limits its generalisability (Nematy et al., 2006). Additionally, whilst the study analysed energy requirements according to basal metabolic rate (BMR), newer guidelines developed by the British Dietetic Association (BDA) and the Parenteral and Enteral Nutrition Specialist Group (PENG) state that resting energy expenditure (REE) is a more appropriate measure in estimating the nutritional requirements of adults when acutely unwell (Todorovic and Mafrici, 2018).

The standard approach in hospital for monitoring in-patient dietary intake is a visual estimation method (VEM), such as a ‘quarter’ or ‘half’ of a meal or expressed as a percentage (Heighington-Wansbrough and Gemming, 2022). However, the validity of this method is questionable on account of the potential for inaccuracy and variability between staff. In a systematic review of 14 studies using varying VEM methods, underestimation ranged from <2% to 53% in 5 studies, and overall, training was identified as a crucial factor in relation to compliance and accuracy (Hirsch et al., 2021). Although a weighed food diary was cited as the ‘gold standard’ for measuring dietary intake, in a ward context, this can be an arduous task.

Dietary intake in the immediate post-operative period is crucial in the care of surgical patients, on account of an altered metabolic state attributed to preoperative fasting, combined with an inflammatory response provoked by the trauma of injury (Hirsch et al., 2021). As opposed to minimally invasive surgery, a hip fracture repair requires a traditional ‘open’ approach that can exacerbate the surgical stress response, increase nutritional needs and prolong recovery. The preservation of muscle mass and meeting whole-body macronutrient energy needs is crucial following a hip fracture repair to allow for mobilisation. In a systematic review of 16 studies of hip fracture outcomes, early mobilisation resulted in a reduction in post-operative complications and length of hospital stay (LOS) (Aprisunadi et al., 2023). More specifically, protein and carbohydrates are crucial at each stage of perioperative care, of which carbohydrates are key to offset the effects of preoperative hypermetabolic catabolism as seen with preoperative fasting or in the presence of malnutrition, that subsequently, necessitates increased protein intake to offset muscle atrophy due to reduced mobility and surgical stress (Hirsch et al., 2021).

Overall, there is currently a lack of robust research concerning the specific post-operative dietary intake of older adult hip fracture patients. Whilst varying supplementation methods could be beneficial for those identified as malnourished, specific guidance regarding their nutritional management is limited. Therefore, it is warranted to observe post-operative dietary intake in the first instance, where there is potential to identify specific areas where recommendations for practice could be made.

### Research aims

The primary aim is to observe if the post-operative dietary energy intake (kJ/kcal) of older adult hip fracture patients meets their REE needs that would allow for basic movements, such as from bed to chair and initial mobilisation with a physiotherapist post-surgery.

Secondly, the aims of the study are to explore if there is a correlation between post-operative dietary intake and LOS; to explore the relationship between comorbidity (where reported) and post-operative dietary intake, according to dietary intake; and to explore (if) in the development of post-operative complications (including, delirium, infection, pressure ulcers and venous thromboembolism), there is a correlation with post-operative dietary intake.

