#### Dietary intake

We will analyse if dietary intake is sufficient to meet estimated REE requirements and explore the effect of dietary intake as a predictor of LOS and post-operative complications. Current guidelines will be used to calculate REE, and we will use a factor of 23 kcal/kg actual body weight per day for ‘surgical fixation of a hip fracture’ according to the supporting evidence-based recommendations specified in the guidelines (Todorovic and Mafrici, 2018). Using macronutrient data for hospital meals provided by the trust, consumption and waste per meal will be calculated according to energy (kJ/kcal), protein, carbohydrates, fats and fibre. For any snacks consumed or foods not listed by the hospital, Nutritics v6.00 software will be used for macronutrient data (Nutritics, 2024).

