### Data storage and analysis

Participant identifiable data (name, date of birth and hospital number) will be used to create a unique identifier that will ensure the correct food diary data is recorded against the correct patient, when accounting for a participant's potential movement between rooms during their ward stay. Once the participant's LOS and discharge destination data has been obtained, the participant's data will be anonymised and assigned a unique reference number. All participant data will be recorded and held within the trust site to maintain confidentiality and the transfer of patient information once assigned an identifier will be from the research department to the researcher's secure email.

Baseline nutritional requirements for REE, total energy expenditure (TEE), protein, carbohydrates and fat nutritional requirements per day will be calculated according to the specific guideline formula (Todorovic and Mafrici, 2018). In the instance where BMI is outside of the range 18.5 to 30 kg/m^2^, calculation adjustments will be made as per the guideline recommendations (Todorovic and Mafrici, 2018). Regarding physical activity and diet-induced thermogenesis (PAL), a combined factor range of 1.0 to 1.10 will be used, which the guidelines state is a ‘post-surgery factor’ (Todorovic and Mafrici, 2018). In cases where there is a range specified, calculations of nutritional requirements will be made at both the lower and higher scale. Demographic variables will be presented in descriptive summaries such as mean ± SD and median for continuous variables and percentages for categorical variables. For statistical analysis we will present descriptive statistics for REE met per day and to make inferences, we will take an average of the proportion of REE intake of the total food diary.

Multiple regression analysis will be used to explore if REE is a predictor of LOS, with post-operative complications and medical history used as confounders along with those who have capacity or not. Due to a small sample size, we acknowledge that caution should be taken with secondary subgroup analysis. In addition, where REE is met or exceeded, participants food diaries will be scrutinised to explore if this is attributed to a specific category of food (e.g. a high-fat dessert item) and where REE is not met, food diaries will be scrutinised to explore if this is related to complications reported.

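### The primary aim is about energy to mobilise, but intake is compared only with resting expenditure; the total expenditure that is also calculated is given no stated role

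*Protocol article*

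**What the plan says.** The Research aims section asks whether post-operative energy intake "meets their REE needs that would allow for basic movements, such as from bed to chair and initial mobilisation with a physiotherapist post-surgery". The Abstract puts it more briefly: whether intake "meets their post-operative REE needs to mobilise post-surgery".

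The comparator is named in several places, and each time it is REE:

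- **Hypothesis:** patients are expected to fall short of their daily REE needs.
- **Dietary intake:** "We will analyse if dietary intake is sufficient to meet estimated REE requirements", with REE taken as 23 kcal per kg actual body weight per day.
- **Data storage and analysis:** description is of REE met per day, and "to make inferences, we will take an average of the proportion of REE intake of the total food diary". The split that decides how food diaries are examined is also REE met or not met.

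The same section treats REE and TEE as different quantities: "Baseline nutritional requirements for REE, total energy expenditure (TEE), protein, carbohydrates and fat nutritional requirements per day will be calculated". Activity and digestion enter through their own multiplier: "Regarding physical activity and diet-induced thermogenesis (PAL), a combined factor range of 1.0 to 1.10 will be used". Where a range applies, "calculations of nutritional requirements will be made at both the lower and higher scale". The article states no comparison of intake with TEE.

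**The concern.** In the plan's own scheme, energy for movement belongs to the activity and thermogenesis factor, and so to TEE. The aim nevertheless attaches movement and first mobilisation to REE, and the stated analysis stops at REE. The question asked and the yardstick used are therefore different.

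What is at stake is the meaning of a favourable result. If patients average at or above 100% of REE, the aim as worded invites the conclusion that they had enough energy to mobilise. At the upper end of the plan's own range, that conclusion could be wrong for patients just above REE. The Discussion hopes the results will support staff education and training, so the wording of the conclusion has consequences.

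This is not a detail left to a fuller document. The article names its comparator repeatedly, and that comparator does not match the aim.

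**Working it through.** There is no planned figure to reproduce: the sample of 30 rests on admissions and funding, and no threshold for the proportion meeting needs is given. The check is arithmetic on the plan's own factors, followed by an illustration.

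**Inputs from the protocol article**

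- REE = 23 kcal/kg/day (Dietary intake).
- Combined activity and thermogenesis factor = 1.0 to 1.10 (Data storage and analysis).
- n = 30 (Study sample).

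**Assumptions**

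- TEE = REE × factor. The multiplicative form is inferred from the word factor.
- Body weights are illustrative.
- The guideline adjustment for BMI outside 18.5 to 30 kg/m² is not modelled, because the guideline is not shown.

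**Step 1: requirement per kg.** At 1.0, TEE = 23 × 1.0 = 23.0 kcal/kg/day, the same as REE. At 1.10, TEE = 23 × 1.10 = 25.3 kcal/kg/day. The largest gap is 2.3 kcal/kg/day.

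**Step 2: requirement per patient.**

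| Assumed weight | REE (kcal/day) | TEE at 1.10 (kcal/day) | Gap (kcal/day) |
|---|---|---|---|
| 50 kg | 1150 | 1265 | 115 |
| 60 kg | 1380 | 1518 | 138 |
| 70 kg | 1610 | 1771 | 161 |

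**Step 3: the same intake on the two scales.** Intake at exactly 100% of REE is 100/1.0 = 100% of TEE at the lower end and 100/1.10 = 90.9% at the upper end. To reach the upper TEE a patient needs 110% of REE. The band where the two yardsticks disagree is 100% to just under 110% of REE.

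**Step 4: how many of 30 might fall in that band.** The article does not predict mean intake or its spread, so both are assumed. Let patient-average intake as a percentage of REE be normal with mean m and SD s. The expected number is 30 × [Φ((110 − m)/s) − Φ((100 − m)/s)]. For example, with m = 90 and s = 25 this is 30 × [Φ(0.8) − Φ(0.4)] = 30 × 0.133 = 4.0.

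| Assumed mean, % of REE | SD 15 points | SD 25 points |
|---|---|---|
| 60 | 0.1 | 1.0 |
| 80 | 2.1 | 2.9 |
| 90 | 4.8 | 4.0 |
| 100 | 7.4 | 4.7 |

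The Introduction gives some orientation. One earlier study found 59% of energy needs met, which would put the answer in the first row. A short report gives an SD of 354 kcal/day, which is 354/1380 = 25.7 points of REE at 60 kg, close to the larger SD used here. That SD comes from lunch and dinner in 15 patients, without fluids, so it is only a rough guide to the spread of a multi-day average of all intake.

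**Step 5: direction.** TEE is never below REE for a factor of 1.0 or more. A patient who fails REE therefore fails TEE, and only patients classed as meeting REE can change class.

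**The case against.** The strongest case on the other side has five parts.

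1. **At a factor of 1.0, TEE equals REE.** A reader might infer that a patient at 100% of REE has, on the plan's formula, nothing left for movement or digestion. The document does not support that across its range: at the lower end such a patient meets TEE in full. The disagreement exists only above 1.0 and is at most 10%. This stands. It does not remove the mismatch, because the plan commits to calculating both ends while its stated comparison corresponds to the lower end alone.

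2. **The hypothesis is that patients will not meet REE.** Failing REE implies failing TEE, so REE is the conservative yardstick for that hypothesis. This stands in full.

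3. **The number affected may be close to zero.** A reader might settle on about 4 of 30, but that figure needs a mean intake of about 90% of REE, which nothing in the article supports. At the 59% of needs quoted in the Introduction it is about 0 to 1. This stands as a limit on the size. The care pathway does require two oral supplements a day for all patients, so the mean in this cohort is not known in advance.

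4. **No share of patients with enough energy to mobilise is a planned statistic.** The plan describes REE met per day and an average proportion of REE, and the met or not met split only directs the diary review. One common multiplier for all patients would leave correlations and regression tests of that proportion unchanged. This also stands: the issue concerns what the primary description may be said to show, not the secondary associations.

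5. **The factor of 23 kcal/kg might already cover movement, or the full plan might tabulate TEE.** Nothing in the article says so. It introduces 23 kcal/kg as the basis for REE and then provides a separate factor for activity. Its preference for REE in the Introduction is over basal metabolic rate, not over TEE.

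**Conclusion.** The mismatch is real on the document's own terms. The aim concerns energy that allows movement and mobilisation, every stated comparison is with REE, and TEE is calculated without a stated use in judging intake. The two requirements differ by 0 to 2.3 kcal/kg/day, or 0 to 138 kcal/day at an assumed 60 kg.

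The consequence is one-sided. Conclusions that needs are not met stand; only a conclusion that patients had enough energy to mobilise can be too favourable. The number of patients in the disputed band runs from about 0 to 1 of 30 at a mean of 60% of REE to about 4 to 7 of 30 at means of 90 to 100%. These counts rest on an assumed normal distribution, assumed means and SDs, and a multiplicative factor. The mismatch itself needs none of them.

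A reader might infer that only the 1.10 value can support a statement about mobilisation. That goes further than the document allows, because the plan deliberately spans a range taken from a guideline not shown here. Severity is moderate: worth correcting before analysis, but not a flaw that invalidates the primary result.

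**What to change.** Either of two changes resolves it.

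- **Keep the mobilisation question.** Report percentage of TEE met at both 1.0 and 1.10 beside percentage of REE. The 1.0 column will equal the REE column if TEE is a simple multiple, and a note can say so. Base any statement about energy for mobilisation on the TEE range, and say explicitly when the conclusion differs between its two ends. Keep percentage of REE as the description of resting needs.
- **Keep REE as the only comparator.** Remove the movement and mobilisation wording from the aim in the Abstract and in Research aims, and limit the conclusion to resting needs.

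Neither needs new data, since TEE is already to be calculated. The first costs a little extra tabulation, and at the upper end the mean percentage of requirement met is lower by 1 − 1/1.10, about 9% in relative terms. That 9% applies to the percentage of requirement met, not to the share of patients meeting it. The second costs only wording, at the price of a narrower claim.

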### Hypothesis

We hypothesise that older adult hip fracture patients will not be meeting their daily REE needs.We hypothesise that a reduced dietary intake due to participants being unable to meet their daily REE needs because of trauma, anaesthesia and surgery will have a negative impact on LOS and post-operative complications.We hypothesise of an association between reduced dietary intake and a combination of nausea, delirium and pain.To our knowledge, this is the first study to use a weighed food diary for older adult hip fracture patients from the day of surgery (day zero) to post-operative day three inclusive that will not require patient or ward staff recall. With data collection being conducted directly by the researcher, this will increase the accuracy of recording dietary intake.

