## Methods

### Design

The design is a prospective study using a convenience sampling method. The novelty of this study is grounded in the approach of a post-operative weighed food diary. Rather than participant recall, ward staff recall or asking ward staff to weigh food (which was not feasible due to ward staff workload), the researcher will weigh and record the participants dietary intake which will therefore increase the accuracy of the data obtained.

Using this design and methodological approach may offset potential refusal to participate in the study as there is no foreseeable risks to the participant nor burden which could potentially lower attrition risks. The design of this study is aimed at exploring biopsychosocial factors associated with older adult hip fracture patients’ outcomes in relation to LOS and post-operative complications. In particular, the inclusion of participants that lack capacity and/or in the presence of comorbidity could provide crucial insight to a subgroup of an at-risk population that has been previously excluded. The study will be conducted in one phase of 4 weeks. Participants enrolled on the study will not be able to obtain their data after the study has been completed as they will be anonymised and assigned a unique reference number after LOS and discharge destination data has been obtained. With no second phase of the study, participants’ identifiable data will not be retained for future research purposes.

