### Food diary protocol

The weighed food diary will commence on the participants day of surgery (day zero) and will conclude at post-operative day three inclusive. The weighed food diary will consist of the researcher using an electronic digital kitchen scale with a weight graduation of 1 g (AccuWeight 201, maximum weight 5 kg) to weigh all items served to the participant before and after their mealtime. The researcher will not serve any food directly, with plates or bowls placed directly on the digital scale and recorded by the researcher. Should a food be packaged with a specified weight – for example a yoghurt, said weight on the packaging will be recorded. Fluid intake will be recorded according to each mealtime (e.g. a cup of tea or fruit juice) and the researcher will liaise with the ward staff to log how many jugs of water the participant has consumed daily, and if this has been accompanied with other items such as cordial. A baseline measurement of water jugs, cups and beakers will be taken prior to the study commencing.

The researcher will not be present nor disrupt the participant during their meal, and after their food tray has been retrieved, the researcher will weigh the plate if it is a complete meal (e.g. lasagne), or, if it is a multiple item meal (e.g. meat, potatoes and vegetables), the researcher will weigh the leftover components individually to ensure the validity of the weighed food method and to achieve the highest degree of accuracy possible. After mealtime has concluded, the researcher will briefly ask the participant if they have had any snacks between their meals. Any observed assistance with meals (such as a family member) will be confirmed with ward staff. Additionally, as part of the specific NOF pathway in place, all hip fracture patients regardless of MUST screening assessment are required to consume two oral nutritional supplements (Nutricia™ Fortisip Compact or Fortisip Compact Protein) daily. The researcher will liaise with the ward staff regarding consumption and additionally will record the amount consumed. Data will also be collected regarding the times of meals and the ratio of staff to patients on the ward during each mealtime.

The researcher will liaise daily with the participant's named nurse regarding complications that may develop post-operatively during the study period, such as delirium, pressure ulcers, infection and venous thromboembolism.

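### The weighed diary is said to need no patient or staff recall, but snacks, cordial and at least part of supplement intake rest on report

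*Protocol article*

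**What the plan says.** Two places in the protocol article rest the accuracy of the diary on avoiding recall. The Hypothesis section describes a diary from the day of surgery to "post-operative day three inclusive that will not require patient or ward staff recall". The Design section sets researcher weighing against the alternatives: "Rather than participant recall, ward staff recall or asking ward staff to weigh food".

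The Food diary protocol describes the actual sources:

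- Meals: the researcher uses a scale "to weigh all items served to the participant before and after their mealtime". Packaged food is entered at its label weight.
- Mealtime drinks: "Fluid intake will be recorded according to each mealtime".
- Water between meals: "the researcher will liaise with the ward staff to log how many jugs of water the participant has consumed daily", together with any additions such as cordial.
- Snacks: after the meal, "the researcher will briefly ask the participant if they have had any snacks between their meals".
- The two daily oral nutritional supplements, which the site pathway requires for every hip fracture patient: "The researcher will liaise with the ward staff regarding consumption and additionally will record the amount consumed".

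The primary aim (Research aims) compares energy intake with REE. REE is set at 23 kcal per kg of actual body weight per day (Dietary intake).

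**The concern.** The property that the article gives as its novelty is not one that its own method has. Snacks depend on what the patient reports. Cordial, and at least part of supplement intake, depend on what ward staff report. All of these supply energy, so they belong to the numerator of the primary comparison.

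Two consequences follow. First, readers of the results would take the whole intake figure as weighed when part of it is not, or is not stated to be. Second, the snack question is least reliable in patients who are confused. The Design section deliberately includes participants who lack capacity, and delirium is one of the complications studied. The Hypothesis section expects lower intake to go with a combination of nausea, delirium and pain. If confused patients leave out snacks they have eaten, their recorded intake falls, and the expected association could appear or be exaggerated. No other way of finding out about snacks is described for patients who cannot answer reliably.

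**Working it through.** **Consistency check, item by item (Food diary protocol)**

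| Item | Stated source | Carries energy? | Consistent with no recall? |
|---|---|---|---|
| Food served at meals | Scale, before and after | Yes | Yes |
| Mealtime drinks | Recorded per mealtime; no recall mentioned | Some | Not contradicted |
| Water jugs | Ward staff | No, if plain water | No, but no effect on energy |
| Cordial and other additions | Ward staff | Yes | No |
| Between-meal snacks | Participant | Yes | No |
| Two daily supplements | Ward staff, plus an amount recorded by the researcher in an unstated way | Yes | Not as written |

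**Size of the supplement component**

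The article gives no figure to reproduce here.

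- From the article: 2 supplements per day; REE = 23 kcal/kg/day.
- Assumed, because the article does not give them: energy per supplement E = 100 to 300 kcal; body weight 45, 60 or 75 kg.

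REE = 23 × kg, which is 1,035, 1,380 and 1,725 kcal/day.

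Share of REE if both are taken in full = 2E / (23 × kg):

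- 60 kg: 200/1,380 = 14.5%; 600/1,380 = 43.5%.
- Lowest in the range (75 kg, E = 100): 200/1,725 = 11.6%.
- Highest in the range (45 kg, E = 300): 600/1,035 = 58.0%.

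As a share of intake, take the 643 kcal/day that the Introduction cites for lunch and dinner without fluids, and add the supplements:

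- Fully taken: 200/(643 + 200) = 23.7% to 600/(643 + 600) = 48.3%.
- Half taken: 100/(643 + 100) = 13.5% to 300/(643 + 300) = 31.8%.

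These are the sizes of a component, not of an error. As an illustration of error, suppose one whole supplement is wrongly logged as taken, or as not taken, on one day for a 60 kg patient. That day moves by 100/1,380 = 7.2 to 300/1,380 = 21.7 percentage points of REE. The plan averages over the whole diary (Data storage and analysis), which covers four days from day zero to day three. The patient's average therefore moves by a quarter of that, 1.8 to 5.4 points.

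The energy from snacks and cordial cannot be sized from the article. The snack bias can be given a plausible direction but no magnitude.

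**The case against.** In support of the plan, it can be said that the no-recall sentence is merely too absolute, and that the weighing method for meals is sound. The researcher also records the supplement amount, possibly by weighing. Supplements served with meals may already fall under the rule that everything served is weighed. The diary chart, which is mentioned under Covariates but not shown, may settle the detail. Much of this stands: the supplement amount can only be called not stated to be weighed. It does not rescue the snack question, which is patient report in plain terms, or the use of ward staff for cordial.

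A reader might infer several stronger points that the article does not support:

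- *That a large share of the primary outcome is unweighed.* The method for the supplement amount is unstated, the energy content is not given, and the share varies widely over the assumed range.
- *That drinks in general are recalled.* Mealtime drinks are not described that way, and plain water adds no energy.
- *That the Introduction itself condemns this source.* Its remark that "the validity of this method is questionable on account of the potential for inaccuracy and variability between staff" concerns visual estimation of portions eaten, not asking about snacks or jugs.
- *That supplement error differs by patient cognition.* The informant there is ward staff, and nothing shows that their reports vary with the patient's state. The differential argument applies to snacks only.
- *That capacity groups are compared.* Capacity is listed as a confounder in the length-of-stay regression. It is delirium that is examined against intake.
- *That the activity factor of 1.0 to 1.10 is a yardstick for the error.* The primary comparison is with REE, so it is not.

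**Conclusion.** The contradiction is real. The Hypothesis and Design sections claim independence from patient and staff recall, and the Food diary protocol relies on both for items that count towards the primary energy total. Supplements are the only item whose possible size can be shown. If fully taken, they are 14.5% to 43.5% of REE at 60 kg and 11.6% to 58.0% over 45 to 75 kg, on an assumed 100 to 300 kcal each. The component is not negligible anywhere in that range. How much of it is mismeasured is unknown, and if the researcher does weigh it the problem shrinks to snacks and cordial. Under-reporting of snacks by confused patients is a plausible source of bias towards the hypothesised link with delirium, but it cannot be quantified. The study remains feasible. What needs correcting is the measurement of these items and the claim made for it.

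**What to change.** 1. In the Food diary protocol, state how the supplement amount is measured. Have supplement bottles, and snack remainders or wrappers, kept at the bedside where possible, and let the researcher weigh them on the existing scale at the existing meal rounds.
2. Mark in the diary each item known only from the participant or ward staff.
3. Report the proportion of REE met with and without the report-only items, as a sensitivity analysis beside the main result on total intake. This shows how far the result depends on report. It cannot recover snacks that nobody mentioned, which is why keeping wrappers matters most for participants who are confused.
4. In the Hypothesis and Design sections, limit the no-recall statement to what is actually weighed.

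The cost is a little more researcher time at each round and the cooperation of ward staff in not discarding containers. Staff are not asked to weigh anything, which the Design section ruled out because of workload. Nothing in patient care changes.
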